**Background**

Premature ejaculation (PE) is a common male sexual dysfunction [1], with a global prevalence rate of approximately 20%-40% among adult males. PE negatively impacts the quality of patients' sexual life, affects their emotions, and may even lead to the development of psychological disorders, exacerbating the symptoms of premature ejaculation and creating a vicious cycle. The definition of premature ejaculation has been a subject of controversy [2]. In 2014, the International Society for Sexual Medicine (ISSM) defined premature ejaculation based on evidence-based research [3]: ejaculation always or nearly always occurs prior to or within approximately 1 minute of vaginal penetration (primary premature ejaculation), or clinically, the average intravaginal ejaculatory latency time (IELT) is significantly and distressingly reduced to about or less than 3 minutes (secondary premature ejaculation); in all or nearly all instances of vaginal penetration, ejaculation cannot be delayed or controlled, resulting in negative consequences such as distress, frustration, a sense of inadequacy, and avoidance of sexual contact. Overall, premature ejaculation encompasses three aspects: ejaculation occurring too early, poor ejaculatory control, and the presence of negative consequences.

Waldinger et al. [4] classified premature ejaculation (PE) based on etiology into two primary categories: lifelong PE (LPE) with a prevalence of 2.3% and acquired PE (APE) with a prevalence of 3.9%. In addition, there are two special types: natural variable PE (NPE) with a prevalence of 8.5%, and subjective PE/premature-like ejaculatory dysfunction (SPE) with a prevalence of 5.1%. In China, individuals with a complaint of PE account for approximately 26.0% of the population, with the prevalence of LPE being 12.3%, APE 18.8%, NPE 41.1%, and SPE 24.8% [5].

Urologists or specialists in sexual medicine are usually the first healthcare professionals consulted by patients with premature ejaculation. The diagnosis and evaluation primarily involve history taking, physical examination, ancillary investigations, scale assessments, and intra-vaginal ejaculation latency time (IELT) assessment. Among these, scales or questionnaires are the most widely used tools in clinical practice, providing reliable, interpretable, and standardized means of assessing and differentiating premature ejaculation. The Premature Ejaculation Diagnostic Tool (PEDT) is the most commonly used scale. Ancillary investigations mainly focus on determining the presence of comorbid conditions such as chronic prostatitis, erectile dysfunction, or endocrine disorders.

The etiology of premature ejaculation has not been definitively determined, leading to a variety of treatment approaches. Recent literature on premature ejaculation treatment can be classified into the following categories: psychological therapy, behavioral therapy, surgical treatment, local anesthesia medication, oral medication, and local treatments. Psychological therapy includes personalized interventions such as sexual health/technique knowledge education, psychological support, and cognitive improvement. Behavioral therapy typically involves gradually increasing levels of genital stimulation to help men better control ejaculation behavior. Local anesthesia can effectively increase the threshold of penile sensation, reduce penile sensitivity, improve IELT (intra-vaginal ejaculation latency time), and alleviate premature ejaculation symptoms. Oral medications include selective serotonin reuptake inhibitors (SSRIs) such as dapoxetine, tricyclic antidepressants (TCAs), phosphodiesterase-5 inhibitors (PDE-5i), alpha-blockers, and traditional Chinese medicine, which can improve symptoms. Local treatments involve external application of Chinese herbal medicine, electrophysiological therapy, and other methods. Surgical treatment is not recommended by the European Association of Urology, but clinical options may include procedures such as circumcision and selective dorsal neurectomy.

In recent years, several clinical studies in China have explored disease remote management using WeChat technology [6,7,8,9,10], including cardiovascular diseases, endocrine disorders, and postoperative urological rehabilitation. The results of these studies have shown that a patient-centered remote management model, based on in-hospital treatment and strengthened outpatient management, has improved treatment effectiveness and clinical outcomes to some extent compared to traditional conventional treatment models. Premature ejaculation is also a disease that relies on in-hospital treatment with auxiliary outpatient management. However, research exploring remote management for premature ejaculation in China is still lacking. This study aims to observe the clinical impact of remote management on premature ejaculation patients undergoing conventional treatment, explore suitable means and application scenarios for remote management, and provide references for the development of guidelines, consensus, and standards for remote management of premature ejaculation.

**Objectives and Outcomes**

Aim 1: To determine the efficacy of mobile-based CBT intervention compared to conventional treatment for patients with premature ejaculation (PE).
- Hypothesis 1a: a significant difference in the mean scores of the premature ejaculation diagnostic tool (PEDT) is expected between the two groups within 8 weeks.

Aim 2: To determine whether the duration of mobile-based CBT intervention has an impact on the efficacy for patients with PE.
- Hypothesis 2a: some significant differences in the PEDT scores, intravaginal ejaculatory latency time (IELT), and the Female Sexual Distress Scale-Revised premature ejaculation version (FSDS-R-PE) scores are expected between the two groups at 4 and 8 weeks.

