**Trial design**

This study is a multicenter, randomized, controlled, open-label parallel-group exploratory trial, consisting of an intervention group and a standard treatment group. Participants will be randomly assigned in a 2:1 ratio to evaluate the efficacy of CBT in improving ejaculatory control in patients with PE. The study will be conducted from May 2023 to Dec 2024 at ten hospitals in China, primarily including the First Affiliated Hospital of Sun Yat-Sen University. The study protocol follows the Standard Protocol Items: Recommendations for Interventional Trials (SPIRIT).

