**Group therapy**

Designated personnel at the trial center will input basic information of eligible patients into the randomization system according to the randomization table. A random number will then be generated. Patients who meet the inclusion criteria will undergo random allocation after obtaining signed informed consent.

Both patient groups received conventional treatments, including chemotherapy, traditional Chinese medicine, and instrument therapy, with treatment selection and plans based on the guidelines for diagnosis and treatment of premature ejaculation. To maximize the effectiveness of CBT interventions based on mobile devices in PE patients, we used remote management through social media software (WeChat) to address sensitive issues that may be difficult to reach in the population. We used the WeChat-MiniApp: "PE-CBT" developed by Hangzhou Kang Ming Information Technology Co., Ltd. to remotely manage the intervention group of patients. WeChat management mainly includes: (1) patients can achieve out-of-hospital coordination and management through WeChat and learn courses on cognitive-behavioral therapy; (2) researchers can track patient management through outpatient clinics (Fig 1). The specific course schedule is shown in the Fig 2. The entire course is divided into three stages. The stage 1 focuses on improving cognition, the stage 2 focuses on improving behavior, and the stage 3 focuses on reviewing.

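### Aim 2 asks whether CBT duration affects efficacy, but the text assigns no one a different course length and Hypothesis 2a never contrasts week 4 with week 8

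*Protocol*

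**What the plan says.** Under Objectives and Outcomes, Aim 2 is "To determine whether the duration of mobile-based CBT intervention has an impact on the efficacy for patients with PE". Its only hypothesis, 2a, names PEDT, IELT and FSDS-R-PE, whose "scores are expected between the two groups at 4 and 8 weeks". The secondary outcome list repeats the same three measures at the same two times.

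Trial design describes a study "consisting of an intervention group and a standard treatment group" and says: "Participants will be randomly assigned in a 2:1 ratio to evaluate the efficacy of CBT". No further randomisation, to course length or anything else, is mentioned.

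Group therapy describes one course: "The entire course is divided into three stages". The content changes as the course proceeds: "The stage 1 focuses on improving cognition, the stage 2 focuses on improving behavior, and the stage 3 focuses on reviewing". On timing the text says only "The specific course schedule is shown in the Fig 2", and that figure is not available here. The section on compliance asks intervention patients to complete the learning as required. Both arms receive conventional treatment. Data processing and storage sets the follow-up assessments at 28±2 and 56±2 days, with no different schedule for either arm.

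**The concern.** An aim about duration needs patients who differ in duration for a reason the trial controls, or at least a stated contrast that bears on duration. The protocol text offers neither. Hypothesis 2a asks whether the arms differ at each of two visits. That is the efficacy question of Aim 1 put twice and extended to two more measures.

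What is at stake is interpretation. With Aim 2 worded as it is and two separate comparisons beneath it, the natural way to answer the aim is to see which visit reached significance. A difference at week 8 but not at week 4 would then look like evidence for longer CBT, even if the true effect were the same at both visits.

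**Working it through.** The protocol gives no figure for this point, so there is none to reproduce. The check has three parts.

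**1. What two arms and two visits can identify.** Take three quantities: an intercept, weeks elapsed and weeks of CBT. Assume that the course runs throughout the 8 weeks, which the text does not state.
- Intervention arm alone: rows (1,4,4) and (1,8,8). The rank is 2 for three parameters, so time and exposure cannot be separated.
- With the control arm, which adds (1,4,0) and (1,8,0), the rank is 3. An additive time effect can be separated from time on CBT.

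Write D4 and D8 for the arm differences at weeks 4 and 8. Effects of elapsed time common to both arms cancel in each. What remains is

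D8 − D4 = (longer course) + (later-stage content) + (delayed effect of what was already given).

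This is one estimable quantity made up of three unknowns. A group assigned a shorter course but assessed at the same late visit would isolate the delayed effect. That group is named only to show what is missing; it is not a proposal. Even then, length and stage content would stay together unless content was also varied.

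**2. Why two separate tests do not measure change.** Inputs, all assumed except that 80% matches the β=0.2 in Sample size: the same true effect at both visits, two-sided 5% tests, and correlation ρ between the two test statistics. At 80% power each statistic has mean 1.96 + 0.84 = 2.80. The chance that exactly one is significant is

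2 × [P(one given visit not significant) − P(neither significant)].

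| Power per visit | ρ | One given visit not significant | Neither significant | Tests disagree |
|---|---|---|---|---|
| 80% | 0.5 | 0.200 | 0.087 | 2 × 0.113 = 23% |
| 80% | 0.7 | 0.200 | 0.113 | 2 × 0.087 = 17% |
| 50% | 0.5 | 0.500 | 0.333 | 2 × 0.167 = 33% |
| 50% | 0.7 | 0.500 | 0.373 | 2 × 0.127 = 25% |

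These come from the bivariate normal distribution. A simulation of 400,000 trials agrees (0.225 and 0.176 at 80% power, 0.334 and 0.253 at 50%). By symmetry, half of the disagreements are significant at week 8 only: about 11% (ρ = 0.5) or 9% (ρ = 0.7) of trials at 80% power.

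**3. The PEDT recall period.** Primary outcome measures says the PEDT covers the past 6 months, about 26 weeks. The week-4 and week-8 windows are 4 weeks apart, so they share 26 − 4 = 22 weeks, or 22/26 = 85%. Taken literally, only 4/26 = 15% of the first window and 8/26 = 31% of the second fall after the start of the intervention. A week-8-minus-week-4 change in PEDT is therefore likely to be damped.

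**The case against.** The strongest reply is that duration here simply means time on treatment. On that reading, the arm difference at two visits is informative, and the control arm removes what the arms share. Much of this stands. A reader might infer that time on conventional treatment, the natural course and repeated questioning all confound the comparison of week 4 with week 8. That holds for a comparison within the intervention arm. It does not hold for the between-arm difference that Hypothesis 2a names, where these largely cancel. But even on this reading the quantity needed is the change in the arm difference, which Hypothesis 2a does not state.

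A reader might also take the word *some* in Hypothesis 2a as a rule that any one significant result among three measures and two times counts as success, and so charge inflated error. The protocol sets no such rule. The hypothesis lists the measures and times jointly, they are secondary outcomes in a trial that calls itself exploratory, and multiplicity handling may be in an SAP that is not shown.

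Two further points stand. The protocol nowhere says it will conclude that longer CBT works better; that is a risk created by the wording, not a stated plan. And that all intervention patients follow one course is read from the text without Fig 2. Finally, the choice of model belongs to an SAP, but an SAP cannot supply variation in duration that the design does not create.

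**Conclusion.** The point holds in a limited form. As written, Aim 2 cannot be answered by the comparison placed under it. The trial can describe whether the between-group effect changes from week 4 to week 8, but it cannot attribute a change to course length rather than course stage or delayed effect. Judging by significance at separate visits would give a spurious contrast between them in about 17% to 23% of trials with an unchanged effect, under the assumed 80% power per visit and correlations of 0.7 to 0.5. At 50% power the range is 25% to 33%.

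The conclusion on identifiability needs none of these numbers. It rests on the text describing a single course, and would need revisiting only if Fig 2 showed assigned variation in length. The primary comparison, the randomisation and the data collected are unaffected. The change should be made because a stated aim would otherwise go unanswered or be answered wrongly.

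**What to change.** - Reword Aim 2 as describing the time course of the between-group effect.
- Replace Hypothesis 2a with one direct estimate, with 95% CI, of the change in the arm difference from week 4 to week 8. Either compare each patient's week-8-minus-week-4 change between arms, or use an arm-by-visit term in a repeated-measures model. Statistical methods names no such model, so it would have to be newly specified.
- Report this contrast for PEDT with a caveat on the 6-month recall period, and give the IELT and FSDS-R-PE contrasts beside it.
- Report the arm differences at each visit, with 95% CIs, as supportive.
- State that no conclusion on CBT duration or dose will be drawn. An analysis by amount of course completed would be observational and should be labelled so.

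The cost is a change of wording and a little more analysis, with no new data. The contrast will be imprecise. With equal variances and complete data its standard error is √(2(1−ρ)) times that of a single-visit difference: 1.0 times at ρ = 0.5 and 0.77 times at ρ = 0.7. The change being estimated is likely to be smaller than the effect itself. The trial also gives up a duration claim, but one that the design could not support.

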**Outcomes**

**Primary outcome measures**

The mean PEDT scores of two groups of patients were recorded within 8 weeks. To assess treatment effectiveness, patients were evaluated using a medical questionnaire during each outpatient/telephone follow-up on day 1, at the end of week 4 and week 8 of the study. The questionnaire consisted of five questions with five different response categories (A=0, B=1, C=2, D=3, E=4) to evaluate the conditions over the past 6 months. Scores <8 indicated no problem; scores between 9 and 10 suggested a need for diagnosis at a hospital, while scores >11 were considered indicative of premature ejaculation. The PEDT scale has been widely used in China and has demonstrated good internal consistency, reliability, and validity. Studies have shown that the scale has good predictive ability in Chinese premature ejaculation patients.

**Secondary outcome measures**

(1) PEDT scores of the two groups at 4 and 8 weeks;

(2) IELT duration of the two groups at 4 and 8 weeks;

(3) FSDS-R-PE scores of the two groups at 4 and 8 weeks.

The FSDS-R-PE is a 13-item questionnaire with 5 response categories for each item (0=never, 1=rarely, 2=occasionally, 3=frequently, 4=always), designed to evaluate the sexual function status of female partners of men with premature ejaculation. A higher score indicates a higher level of dissatisfaction with sexual life.

**Trial design**

This study is a multicenter, randomized, controlled, open-label parallel-group exploratory trial, consisting of an intervention group and a standard treatment group. Participants will be randomly assigned in a 2:1 ratio to evaluate the efficacy of CBT in improving ejaculatory control in patients with PE. The study will be conducted from May 2023 to Dec 2024 at ten hospitals in China, primarily including the First Affiliated Hospital of Sun Yat-Sen University. The study protocol follows the Standard Protocol Items: Recommendations for Interventional Trials (SPIRIT).

**Eligibility criteria**

Patients meeting the following inclusion criteria were recruited: (1) male aged between 18-40 years; (2) in a stable heterosexual relationship with the same partner for at least 6 months; (3) diagnosed with PE according to the ISSM definition and not medically managed for at least 7 days; (4) able to use mobile devices such as smartphones and tablets; and (5) having read and agreed to sign the informed consent form.

Patients' exclusion criteria are as follows: (1) primary premature ejaculation patients; (2) patients taking medications such as amphetamines, dopamine, etc. that may cause PE; (3) patients with cognitive impairment, communication disorders, visual impairment, hearing impairment; (4) patients with other complex male genital diseases; (5) patients with malignant tumors; (6) patients participating in other clinical trials; (7) patients deemed unsuitable for this study by the researchers. This trial does not involve exploration of drug/medical device interventions.

Participants will be considered for withdrawal from the study under the following circumstances. However, even if participants do not withdraw their consent to participate in the study, they will no longer be considered as trial subjects and will not be included in the analysis of the study as soon as they withdraw from treatment under the following circumstances:

(1) If participants voluntarily withdraw (including dropping out, actively withdrawing, etc.);

(2) If the researcher requires the participant to withdraw due to disease deterioration or other reasons;

(3) If the researcher considers the participant no longer suitable to continue participating in the study.

The researchers will conduct preliminary eligibility screening and collect written informed consent from selected participants prior to baseline evaluation. If data collection is not included in the initial informed consent process of the main clinical trial, each participant in the ancillary study must sign a consent form.

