**Sample size**

This study adopted two control groups, namely, the remote management + conventional treatment group and the conventional treatment group, with a 2:1 ratio for enrollment. The primary research indicator was the PEDT score, with α=0.05 and β=0.2. Previous literature has shown that the PEDT score decreases by at least 2-3 points with psychological/behavioral therapy [20] and by at least 6-7 points with drug therapy [21, 22]. Given a maximum follow-up loss rate of 20% for each group, a target sample size of 300 patients, with 150 patients in each group, was determined.

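### Randomised patients who withdraw from treatment are dropped from the analysis even while their consent stands, so the comparison loses the protection of randomisation and may be biased in either direction

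*Protocol*

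**What the plan says.** The rule stands in the withdrawal paragraph of the protocol's Eligibility criteria section. It applies "even if participants do not withdraw their consent to participate in the study". Its consequence is that the patients concerned lose their status in the trial and "will not be included in the analysis of the study as soon as they withdraw from treatment". Three conditions bring it into force:

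- voluntary withdrawal, which expressly covers dropping out;
- "If the researcher requires the participant to withdraw due to disease deterioration or other reasons";
- a further researcher decision: "If the researcher considers the participant no longer suitable to continue participating in the study".

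Four other places bear on the point:

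- Trial design calls the study a "multicenter, randomized, controlled, open-label parallel-group exploratory trial".
- Group therapy and Patient compliance and withdrawal show that only the intervention arm has a three-stage WeChat course, which its patients are urged to complete.
- Sample size works with the premise "Given a maximum follow-up loss rate of 20% for each group".
- Statistical methods plans to count enrolled, excluded and drop-out subjects and to analyse the reasons. It does not say that drop-outs enter any efficacy comparison.

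No section of the protocol defines an analysis of all randomised patients or provides for follow-up after treatment stops.

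**The concern.** Randomisation makes the two arms comparable at entry. That comparability carries over to the result only if the patients analysed are those randomised, or if exclusions are unrelated to outcome and arm. Here they are not. Deterioration of the treated condition lies close to the primary outcome, the PEDT score. Dropping out may reflect lack of benefit or the burden of treatment. The other two routes are researcher decisions, and because the trial is open-label, a researcher who may know the allocation can determine who is analysed.

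The rule also discards data that could be had. It applies to men whose consent still stands and whose PEDT could be taken at the planned week 4 and week 8 contacts. The wording leaves open whether scores recorded before withdrawal are dropped too. On a literal reading, a man who stops in week 5 loses his valid week 4 score.

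At stake is every between-group comparison in the trial: the primary PEDT comparison and the secondary PEDT, IELT and FSDS-R-PE comparisons. The size and sign of the bias cannot be known from the analysed data, and outcomes that were never collected cannot be recovered later.

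**Working it through.** **What can be reproduced.** The plan gives no figure for this bias. It gives a target of 300 and a maximum loss of 20% per group, so up to 0.20 × 300 = 60 randomised patients could be missing from the analysis.

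**Inputs**

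- From the protocol: 300 patients, maximum loss 20% per group, α = 0.05 (taken as two-sided; sidedness is not stated).
- Allocation: the Sample size section states both 2:1 and 150 per group. The figures below use 200/100; 150/150 is given as a check.
- Assumed, because the protocol is silent: withdrawal in each arm (d_app, d_ctl), the number of PEDT points by which withdrawers are worse than completers (g), and the PEDT standard deviation (SD).

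**Bias.** Let m be the completer mean in an arm. The mean of all randomised patients in that arm is (1 − d)·m + d·(m + g) = m + d·g. Dropping withdrawers therefore makes the arm look better by d·g, and

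bias towards the app = d_app·g_app − d_ctl·g_ctl.

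| Withdrawal, app / control | g, app / control | Bias towards the app (points) |
|---|---|---|
| 20% / 10% | 2 / 2 to 4 / 4 | +0.2 to +0.4 |
| 10% / 20% | 2 / 2 to 4 / 4 | −0.2 to −0.4 |
| 20% / 20% | equal | 0 |
| 20% / 20% | 3 / 0 | +0.6 |
| 20% / 20% | 0 / 3 | −0.6 |
| 20% / 0% | 3 / – | +0.6 |

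Equal withdrawal percentages are not enough to remove the bias. The withdrawers must also be equally ill in both arms.

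**Type I error when there is no true effect.** With SE = SD·√(1/n_app + 1/n_ctl), the two-sided rejection rate is P(Z > 1.96 − bias/SE) + P(Z < −1.96 − bias/SE).

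- 20% / 0% leaves 160/100. At SD 4, SE = 4·√(1/160 + 1/100) = 0.510 and bias/SE = 0.6/0.510 = 1.18. The rate is 0.217 + 0.001, about 22%.
- The same case at other SDs: about 35% at SD 3, 16% at SD 5 and 9% at SD 8.
- The same case from 150/150 leaves 120/150 and gives about 23% at SD 4.
- 20% / 10% leaves 160/90. At SD 4, SE = 0.527. A bias of 0.2 gives 6.7% and a bias of 0.4 gives 11.8%. The excess lies on the side of the app.
- 10% / 20% leaves 180/80. At SD 4, SE = 0.537. A bias of −0.2 gives 6.6% and −0.4 gives 11.5%. The excess lies against the app.
- Equal loss with equal severity keeps the nominal 5%.

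**The case against.** The strongest objection concerns direction. A reader might infer that the rule favours the app, because men doing badly on it disappear. The document does not support that as a conclusion. The rule applies to both arms, so control patients who do badly disappear as well, and withdrawal by arm is nowhere given. If the app helps, deterioration withdrawals could be commoner among controls, which would bias against it. The extra course gives one reason why the app arm could lose more men, so the pro-app direction is plausible but no more than that.

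Three narrower objections also stand:

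- It would be wrong to call the analysed group self-selected, since two of the three conditions are researcher decisions.
- Missing lessons is not itself a listed condition. The protocol answers it with reminders, so a man who skips lessons but attends visits is not clearly removed.
- The 2 to 3 point figure in Sample size is a fall in score under psychological or behavioural therapy in earlier literature. It is not a planned between-group difference, so the bias should not be expressed as a share of an expected effect.

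Two defences do not succeed. The first is that analysis sets belong in a SAP, which is not at hand. The protocol does not leave this open: it states the exclusion, and a SAP that analysed all randomised patients would contradict it. The second is that the trial is labelled exploratory. This softens the type I error argument, but Aim 1 is to determine efficacy and the Background intends the results to inform guidelines and standards. A biased estimate matters for both.

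**Conclusion.** The point holds as a defect of known mechanism and unknown sign. The protocol excludes randomised, still-consenting patients from the analysis for outcome-related reasons, partly at the discretion of researchers in an open-label trial, and no other section restores them.

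In the illustrations the bias runs from 0.6 points against the app, through zero, to 0.6 points towards it. With one arm losing 20% and the other 10%, and withdrawers 2 to 4 points worse, it is 0.2 to 0.4 points in one direction or the other. The 22% type I error belongs to an extreme case (20% against 0%, 3 points, SD 4, 160/100 analysed) and falls as the SD rises. All these sizes rest on assumed withdrawal by arm, withdrawer severity and SD; only the 300 and the 20% ceiling are the protocol's. That the rule gives up the protection of randomisation depends on none of these assumptions. The rule should be corrected while outcomes can still be collected.

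**What to change.** Replace the exclusion sentence in Eligibility criteria with wording such as:

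> Participants who stop the app or conventional treatment remain in the trial. Outcomes, at least the PEDT, are still collected at days 28 and 56 unless consent to data collection is withdrawn, and data already collected are kept. The primary analysis includes all randomised participants in their allocated group.

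Keep the completer analysis, labelled as supportive. The missing-data model and the sensitivity analysis for withdrawers can be left to the SAP.

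The cost is a protocol amendment and some extra telephone follow-up, a route that the Outcomes section already foresees for the PEDT questionnaire. FSDS-R-PE after a man stops treatment would need his partner's continued cooperation, which is why the wording makes only the PEDT the minimum. The estimate may turn out less favourable to the app.
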